#### Part 2: screening optimal rolling manipulation pressure

2.4.2

The low, medium, and high pressure levels were determined using the following procedure. Incremental pressure was applied to the marked points of the bilateral lumbar erector spinae using a simulated dynamometer (NK-500). Participants reported their perceived sensation according to the VAS. Pressure values corresponding to VAS 0–3 (low), 4–6 (medium), and 7–10 (high) were recorded separately for the left and right sides as individual reference values. Before the formal measurement, all participants received standardized training on the VAS scoring criteria, with clear explanations of the sensory descriptors corresponding to 0–3, 4–6, and 7–10. The measurement was started only after the participant confirmed their understanding. Each pressure level was measured three times with a 30-s interval, and the mean value was used for subsequent analysis. All measurements were performed by the same trained operator.

A two-way repeated-measures ANOVA was then performed on these reference values to examine the effects of side, pressure level, and their interaction. If neither the side effect nor the interaction reached statistical significance, the reference values of the corresponding pressure levels were pooled across sides; otherwise, the sides were analyzed separately. A one-way repeated-measures ANOVA was then used to evaluate whether the three predefined pressure levels show statistically distinguishable force values on the pooled data. If no significant difference was found, the classification of pressure levels would be re-evaluated.

The fluctuation ranges of the low, medium, and high pressure levels were calculated separately using the 95% confidence intervals: Fluctuation range (%) = (upper limit of 95%CI − lower limit of 95%CI) / (2 × mean) × 100%. The fluctuation range value (in Newtons) was then calculated as the mean multiplied by the fluctuation range percentage. For each pressure level, the lower limit of the interval was calculated as the mean minus the fluctuation range value, and the upper limit of the interval was calculated as the mean plus the fluctuation range value. The high-pressure level was applied strictly within the participant’s pain tolerance, and the operator’s physical capacity was also considered to avoid injury. After the pressure levels were determined, the Novel Pliance-X 32 Expert glove-type pressure distribution measurement system was used to measure the mechanical parameters of the rolling manipulation as an operational reference and to monitor standardization. The system is calibrated once a day before the operation to ensure the accuracy of pressure measurement. After the tuina pressure range is set, subsequent patients are strictly screened according to the “tuina pressure value range”determined by the experiment, and only subjects whose lumbar erector spinae bearing threshold fell within this range are included, and those beyond the range (too high/too low) are directly excluded.

A preliminary study was conducted before the formal trial to determine the washout duration. Six participants with lumbar muscle strain received a single session of rolling manipulation using clinically common parameters (4 kg, 120 times/min, 10 min). The root mean square (RMS) values of surface electromyography (sEMG) from the bilateral erector spinae were recorded before the intervention, immediately after the intervention, and on Days 3, 5, and 7 after the intervention. The RMS values increased immediately after the intervention, declined by Day 3, fell below the pre-intervention level by Day 5, and remained stable on Day 7. No statistically significant differences were observed between the pre-intervention values and those on Days 5 and 7, indicating that muscle activity had reached a stable state within 7 days. Accordingly, the washout period was set to 7 days (Table 1).

**Table 1 tab1:** RMS values of the bilateral erector spinae during the washout observation (*n* = 6).

Side	Baseline	Immediately after intervention	Day 3	Day 5	Day 7
Left (μV)	48.39 ± 19.42	54.37 ± 19.45*	49.64 ± 11.10	42.16 ± 8.67	41.16 ± 4.58
Right (μV)	45.46 ± 14.29	49.92 ± 23.50	48.16 ± 13.46	42.33 ± 11.37	43.10 ± 15.68

**p* < 0.05 vs. baseline. RMS: root mean square, reflecting the intensity of muscle activation. RMS increased immediately after the intervention, declined by Day 3, fell below the baseline level by Day 5, and remained stable on Day 7. The statistically significant increase immediately after the intervention was observed on the left side.

Participants were randomly assigned to one of three intervention sequences: low-medium-high, medium-high-low, or high-low-medium. Taking the low-medium-high sequence as an example, the procedures for the other two sequences (medium-high-low and high-low-medium) were identical, with the only difference being the order of pressure application.

First, surface electromyography, isokinetic muscle strength, muscle tension, pressure pain threshold and VAS indicators of the subjects’ bilateral lumbar regions are detected before the test; then, low-pressure rolling manipulation stimulation is applied to the subjects’ lumbar regions, with the intervention position at the bilateral L1-L5 lumbar erector spinae, repeated intervention from bottom to top for 10 min at 120 times/min; the operators are required to have more than 5 years of clinical experience in TCM tuina and hold a TCM practicing physician certificate. Finally, surface electromyography, isokinetic muscle strength, muscle tension, pressure pain threshold and VAS indicators of the bilateral lumbar regions are detected immediately after the rolling manipulation intervention.

Second, after the completion of the low-pressure rolling manipulation stimulation operation procedure and detection, the subjects enter a washout period. After the end of the washout period, the subjects receive medium-pressure rolling manipulation stimulation, and the operation procedure is the same as that of the low-pressure rolling manipulation stimulation, with the same detection methods and processes for medium and low pressure.

Finally, after the completion of the medium-pressure rolling manipulation stimulation operation procedure and detection, the subjects enter a washout period. After the end of the washout period, the subjects receive high-pressure rolling manipulation stimulation, and the operation procedure is the same as that of the low-pressure rolling manipulation stimulation, with the same detection methods and processes for high and low pressure.

The primary outcomes for screening the optimal pressure are the changes in the surface electromyographic (sEMG) indicators of the bilateral lumbar erector spinae, including the time-domain indicator (root mean square, RMS) and the frequency-domain indicator (median frequency, MF). The final determination of the optimal pressure level will be made by combining these primary outcomes with secondary biomechanical indicators, including isokinetic muscle strength, muscle tension, and pressure pain threshold. The outcomes will be analyzed separately. Differences among the low-pressure, medium-pressure, and high-pressure conditions will first be examined for each outcome. For outcomes showing significant differences across pressure levels, regression analysis will be further performed to examine how the outcomes change across different pressure levels (as detailed in Section 3.10). Correlation analyses will also be performed to examine the relationships among the different biomechanical measures. The final pressure will be selected according to the overall pattern of the sEMG and other biomechanical findings within the predefined VAS tolerance range. A favorable change in a single secondary outcome alone will not determine the optimal pressure.

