This study graded and screened the pressure parameters of the rolling manipulation from a biomechanical perspective, aiming to overcome the subjective limitations of traditional tuina that relies on empirical operation. Existing studies have shown that the core mechanism of massage-like manipulations is closely related to mechanotransduction: mechanical pressure act on the skin, fascia and muscle tissues, and regulate inflammatory responses and pain regulatory pathways through cellular signal transduction (38). The therapeutic effect of manipulations does not simply depend on the magnitude of force, but on the standardized combination of pressure, frequency and duration, and a stronger pressure does not necessarily lead to a better effect (38–40). Studies on tuina for peripheral induced neuropathic pain have also confirmed that appropriate manual stimulation can exert analgesic effects through peripheral anti-inflammation, regulating ion channels and altering central brain function (41). Accordingly, this study defined low, medium and high levels based on individualized pressure calibration combining VAS perception and objective pressure measurements. Optimal parameters are selected using multi-dimensional biomechanical indicators including surface electromyography and isokinetic muscle strength, and standardized monitoring of manipulation parameters is realized via a dynamic pressure distribution measurement system. It is intended to establish a quantitative correlation system of “individual pain threshold-manipulation mechanical parameters-biological effect”, so as to formulate an objective and repeatable pressure standard for the rolling manipulation and solve the key problem of the lack of quantitative specifications for clinical tuina parameters.

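### Section 2.4.2 screens individual patients against the 95% confidence interval of a group mean, a window that does not describe individuals and narrows as more calibration data are collected

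*Protocol article*

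**What the plan says.** Section 2.4.2 first records, for each participant and side, the force that matches three VAS bands (low, medium, high). Sides are pooled if the side effect and the interaction are both non-significant. The section then builds a range for each level:

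- "The fluctuation ranges of the low, medium, and high pressure levels were calculated separately using the 95% confidence intervals", as the CI width divided by twice the mean, in percent.
- "The fluctuation range value (in Newtons) was then calculated as the mean multiplied by the fluctuation range percentage".
- "the lower limit of the interval was calculated as the mean minus the fluctuation range value"; at the other end, the same amount is added to the mean.

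The range is then applied to later patients: "only subjects whose lumbar erector spinae bearing threshold fell within this range are included". Anyone outside it, on either side, is turned away: "those beyond the range (too high/too low) are directly excluded".

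Elsewhere, the extra Part 2 requirements in section 2.2.1 are an age band and a BMI band, with no threshold criterion. Section 2.2.2 says the exclusion criteria are the same in all three parts, apart from the fNIRS item. The Discussion says that "this study defined low, medium and high levels based on individualized pressure calibration", and names VAS ratings and instrument readings of force as the basis.

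**The concern.** A confidence interval for a mean and a range for individuals answer different questions. The first shrinks with the square root of the number measured. The second settles at the spread of the population, however many are measured. Here the first is used where the second is needed, as a hard rule on who enters.

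Two things are at stake. The people studied would cluster around the average threshold, so an optimal pressure chosen from them, or tested in them, would speak mainly for such patients. The strictness of the rule would also depend on how many people happened to be calibrated, which has no bearing on whether a given patient is suitable.

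The rule also sits awkwardly with the rest of the text. It is not among the eligibility criteria, and a group range in newtons is laid over levels that are described as set person by person.

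**Working it through.** **Step 1. What the formula returns.** Let M be the mean and L and U the 95% confidence limits, symmetric about M.

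- Percentage: (U − L) / (2M).
- In newtons: M × (U − L) / (2M) = (U − L) / 2, the half-width of the CI.
- Limits: M − (U − L)/2 = L and M + (U − L)/2 = U.

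Numerical check with arbitrary values M = 50, L = 44, U = 56: 12/100 = 0.12; 50 × 0.12 = 6; limits 44 and 56. The range is the confidence interval itself. This step needs no assumption about the data.

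**Step 2. Share of individuals inside.** The article states no such share, so there is no figure to reproduce. Assumptions: thresholds are normal, the range is that of one level, and n independent values stand behind the CI.

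- Half-width in SD units: h = t(0.975, n − 1) / √n.
- A new patient's distance from the calibration mean has SD σ√(1 + 1/n). The expected share inside is therefore 2 × T[h / √(1 + 1/n)] − 1, where T is the t distribution function with n − 1 degrees of freedom. The SD cancels, so no force data are needed.

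| n | h (SD units) | Inside | Excluded |
|---|---|---|---|
| 6 | 1.049 | 62.4% | 38% |
| 10 | 0.715 | 48.8% | 51% |
| 15 | 0.554 | 40.0% | 60% |
| 24 | 0.422 | 31.7% | 68% |
| 48 | 0.290 | 22.5% | 78% |
| 100 | 0.198 | 15.6% | 84% |

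Worked line for n = 24: h = 2.069 / √24 = 0.422; 0.422 / √(1 + 1/24) = 0.414; share inside 31.7%.

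The value 24 is an assumption. It is the only Part 2 sample size the article gives (section 2.8), and it is the crossover sample, not a stated calibration sample. The value 48 is 24 patients with both sides pooled and treated as independent.

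**Step 3. Sensitivity to shape.** Simulated lognormal thresholds with a coefficient of variation from 0.3 to 0.8, n = 24, leave 32% to 34% inside, close to the normal result.

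**Step 4. Sensitivity to which range is meant.** Suppose the window runs from the lowest level's lower limit to the highest level's upper limit. With level means d SD apart, h = 0.422, and the calibration mean and SD taken as known, the share inside is:

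- for a threshold centred on the middle level, 2Φ(d + h) − 1;
- for one centred on the high level, Φ(h) − Φ(−2d − h).

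For illustrative gaps d from 0.5 to 3, the first excludes from 36% down to about 0%, and the second from 41% down to 34%. The article gives no gap, so these figures show direction only.

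**The case against.** The best defence accepts the algebra and disputes the consequences.

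- **Size.** A reader might infer that the rule necessarily shuts out two thirds of patients or more. The article does not support that. The calibration sample size is not stated, and the loss is 38% at n = 6 and 51% at n = 10. It reaches about two thirds only from roughly 20 to 24 values upward, under a single-level reading. This stands.
- **Which range.** Three ranges are computed, but the screen uses one range and a threshold that is not defined. A low-to-high span is a possible reading and excludes fewer people. Against it, the ranges are calculated separately for each level and no span is described. A reader might also infer that all three ranges must be met at once, but no sentence says so.
- **Which patients.** If the 24 crossover patients supplied the calibration values, the later patients could be those of Part 3. If another group did, n = 24 has no textual basis. This stands as an ambiguity.
- **Recruitment.** A reader might infer that recruitment will fail. At 31.7% inside, 24 / 0.317 gives about 76 otherwise eligible patients measured to admit 24. With no recruitment rate in the article, that shows a screening load, not failure. The 20% allowance in section 2.8 is for attrition, not screen failure.
- **Intended narrowness.** Part 2 is deliberately restricted to limit confounding, and the rule stands next to text on pain tolerance and avoiding injury. A screen may be wanted, and individual calibration can coexist with a group range. That supports having some window, but it does not make the CI of a mean the right one.
- **Loose wording.** The authors may have meant a range of individual values. If so, the printed formula names the wrong interval and still needs correcting.

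**Conclusion.** The point holds in a conditional form. It is certain from the text alone that the range is the 95% CI of the group mean, that it is used to include or exclude individuals, and that it tightens as calibration data grow. This is a printed rule that is statistically wrong, not a detail left to a fuller document.

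The size is conditional. For normal thresholds and one level's range, the expected exclusion is about 38% (n = 6), 51% (n = 10), 68% (n = 24, assumed) and 78% (48 pooled values treated as independent). It is lower if the window is a low-to-high span. Under the single-level reading, findings from the screened patients would apply mainly to people of near-average threshold.

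The absence of the criterion from section 2.2.1 and its uneasy fit with individually calibrated levels are secondary. They call for reconciliation and do not prove an outright contradiction.

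**What to change.** 1. If a screening window is kept, replace the CI of the mean by an interval that describes individuals: a prediction interval, M ± t(0.975, n − 1) × s × √(1 + 1/n), a tolerance interval, or percentiles of the calibration values. At n = 24 the prediction interval is 2.069 × √(1 + 1/24) = 2.11 SD either side. For normal thresholds it covers 95% of new patients in expectation at any n.
2. State how many participants and values stand behind the calibration, and whether sides were pooled.
3. State what the screened threshold is, which level's range (or span) applies, and whether Part 2 patients, Part 3 patients or both are screened.
4. List the criterion in section 2.2.1.
5. Reconcile the group range in newtons with the individual VAS calibration and the tolerance text in section 2.4.2 and the Discussion.

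Whether the screen is needed at all is for the sponsor to settle in that reconciliation. No pressure value or clinical limit is proposed here.

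The cost is one formula, one eligibility line and a few clarifying sentences. The new limits can be computed from the same calibration data. The calibration is reported in the past tense, so if patients have already been screened under the printed rule, the change and its date should be recorded. The downside is a more heterogeneous sample.

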#### Inclusion criteria

2.2.1

The research subjects of this study are divided into a case group and a control group. The case group consists of patients who met the diagnostic criteria for lumbar muscle strain in the General Principles for the Formulation and Revision of Diagnostic and Efficacy Evaluation Criteria for TCM Diseases and Syndromes (No.: ZY/T 10–2024) issued by the National Administration of Traditional Chinese Medicine in 2024 (29). The case groups in the first and third parts needed to meet the following criteria: aged 18–69 years old, regardless of gender; recurrent low back pain for more than 3 months; no other treatment for low back pain received 3 weeks before enrollment; the core area of muscle pain confirmed by physical examination is located in the lumbar erector spinae, ranging from the paravertebral region of the 12th thoracic spinous process to the dorsal surface of the sacrum and the posterior part of the iliac crest; voluntary signing of the informed consent form and cooperation in completing the entire study and providing relevant data. The second part focused on the screening of tuina manipulation pressure, so confounding factors needed to be strictly controlled, and additional requirements are made on the basis of the above criteria: aged 20–40 years old, body mass index (BMI) controlled at 18.5-24 kg/m^2^. The control group is healthy people of the same age group as the case group in the corresponding research part (18–69 years old for the first and third parts, no control group for the second part), without lumbocrural pain symptoms and a history of neuromuscular diseases, who voluntarily signed the informed consent form and cooperated in completing relevant tests.

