#### Exclusion criteria

2.2.2

The contents of the case group and the control group are consistent, and the three parts of the experiment are identical, except that Item (h) is absent in the second part. (a) Patients with mental disorders or impaired consciousness; (b) Pregnant, lactating women and women preparing for pregnancy; (c) Heavy smokers, defined as those smoking at least 20 cigarettes (1 pack) per day; (d) Complicated with non-soft tissue chronic injury diseases such as lumbar intervertebral disc herniation, spinal stenosis and intraspinal lesions; (e) Pain caused by lumbar spine surgery, trauma, rheumatoid arthritis, etc.; (f) Malignant tumors, acute infectious diseases, severe skin diseases, rheumatism and immune diseases, complicated with severe heart, liver and kidney diseases; (g) Patients participating in other external therapies, medications and other treatments that may affect the judgment of results; (h) Contraindications to fNIRS monitoring such as a history of craniocerebral surgery, cranial defects and phobia of headgear wearing.

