#### Part 3: clinical efficacy and cortical hemodynamic responses with optimal pressure

2.4.3

The experiment is divided into three groups, with healthy individuals without lumbocrural pain serving as the healthy control group, who receive intervention using optimal pressure parameters of the rolling manipulation. The protocol is 3 times per week, with one week as one treatment course, for a total of one course (3 interventions). This intervention is administered to investigate cortical hemodynamic changes induced by rolling manipulation with optimal pressure and to assess neuromuscular responses in healthy individuals with intact lumbar muscles, enabling a direct comparative analysis of brain functional and biomechanical responses to the identical manual intervention between healthy subjects and patients with lumbar muscle strain. fNIRS data are collected immediately before, during and after the 1st and 3rd interventions, while muscle tension and pressure pain threshold data are obtained before and after the intervention. Patients with lumbar muscle strain are divided into two groups: a case control group and a case intervention group. The case control group receives health education, whereas the case intervention group receives optimal-pressure rolling manipulation. The health education mainly covers posture management in daily life and work, lumbar protection, and guidance on appropriate physical activity and exercise, with participants’ questions addressed as needed. For both groups, the intervention protocol is 3 times per week, with one week as one treatment course, for a total of two courses. Muscle tension, pressure pain threshold, the Oswestry Disability Index (ODI) and VAS scores are assessed before intervention and immediately after the 1st, 3rd and 6th interventions, at the same detection positions as in Part 1. For the case intervention group, fNIRS data are additionally collected before, during and after the 1st and 3rd interventions. During fNIRS acquisition, participants remained in a prone position with the head and upper chest supported by soft pillows, and the forearms crossed under the forehead to provide additional head support. This posture ensured that the head remained in a relaxed and stable position. The rolling manipulation was applied exclusively to the lumbar region using a smooth, continuous rolling technique without abrupt flicking or plucking motions, thereby minimizing mechanical transmission to the head. The enrollment schedule and assessment protocol are shown in Table 2.

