
**Table 2 tab2:** Study schedule.

Stage	First visit	Pre-intervention	Intervention	Intervention	Post-intervention
Sign informed consent form	X				
Assign group number	X				
Lumbar spine AP & lateral X-ray	X				
Collect basic medical history					
General information	X				
Specialized examination	X				
Clinical DIAGNOSIS	X				
Confirm inclusion criteria	X				
Confirm exclusion criteria	X				
Efficacy observation part 1 trial		Pre-intervention	Intervention	Post-intervention	
Functional near-infrared spectroscopy (fNIRS)		X	X	X	
Muscle tension		X		X	
Pressure pain threshold		X		X	
Visual analogue scale (VAS)			X		
Part 2 trial		Pre-intervention	1st Post-intervention	2nd Post-intervention	3rd Post-intervention
Surface electromyography (sEMG)		X	X	X	X
Isokinetic muscle strength		X	X	X	X
Muscle tension		X	X	X	X
Pressure pain threshold		X	X	X	X
Visual analogue scale (VAS)		X	X	X	X
Part 3 trial		Pre-intervention	1st Intervention	3rd Intervention	6th Intervention
Oswestry disability index (ODI)		X	X	X	X
Functional near-infrared spectroscopy (fNIRS)			Before-during-after	Before-during-after	
Muscle tension		X	X	X	X
Pressure pain threshold		X	X	X	X
Visual analogue scale (VAS)		X	X	X	X
Study evaluation					
Treatment compliance	X				X
Adverse event assessment		X			X
Analysis of dropout reasons					X
Study completion summary					X
CRF statement review					X

To standardize the measurement conditions, all participants in Parts 1, 2, and 3 of the study were asked to maintain their usual daily activity level during the study period and to avoid additional strenuous physical activity. In addition, before each measurement, participants rested in a quiet environment for at least one hour to minimize the acute effect of physical activity on the baseline values.

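### Section 2.4.2 excludes patients by pressure threshold, but the eligibility criteria in 2.2 list no such rule, and as written it cannot be applied

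*Protocol article*

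**What the plan says.** Section 2.4.2 calibrates low, medium and high pressure against VAS bands and turns each level into an interval: "The fluctuation ranges of the low, medium, and high pressure levels were calculated separately using the 95% confidence intervals". It then adds an entry rule. After the range is fixed, "subsequent patients are strictly screened according to the" derived values, "only subjects whose lumbar erector spinae bearing threshold fell within this range are included", and "those beyond the range (too high/too low) are directly excluded".

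The eligibility sections say something else. Section 2.2.2 introduces its list with the statement that "the three parts of the experiment are identical, except that Item (h) is absent in the second part", and items (a) to (h) contain nothing on pressure or threshold. Section 2.2.1 says that for Part 2 "additional requirements are made on the basis of the above criteria", and those requirements are age 20 to 40 years and BMI 18.5 to 24 kg/m² only. For Part 3, section 2.4.3 states that "the case intervention group receives optimal-pressure rolling manipulation" and mentions no threshold screen.

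**The concern.** A patient who meets every criterion in 2.2 but whose threshold lies outside the range is eligible under 2.2 and excluded under 2.4.2. Which population enters Part 2 depends on the section that is followed, and that population is the one in which the optimal pressure is chosen. The rule also leaves open which interval is meant, at which pressure level the threshold is measured, and whose calibration values define the range. If the limits are those of a confidence interval for a mean, they could turn away many ordinary patients for no stated reason.

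**Working it through.** **The texts side by side**

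| Place | What it says on a threshold criterion |
|---|---|
| 2.2.1, all case groups | None |
| 2.2.1, extra for Part 2 | Age and BMI only |
| 2.2.2, items (a)–(h) | None; the lists are declared the same in all parts apart from (h) |
| 2.4.2 (Part 2) | Out-of-range patients excluded outright |
| 2.4.3 (Part 3) | None |

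Section 2.2.2 names (h) as the only difference between parts, and 2.2.1 spells out what is added for Part 2. The 2.4.2 rule fits neither, so 2.2 and 2.4.2 cannot both be complete.

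**What the range is**

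Section 2.4.2 defines the fluctuation percentage as (upper − lower 95% limit)/(2 × mean), multiplies it by the mean to get newtons, and takes the mean plus and minus that value. Write the 95% limits as m − d and m + d.

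- Percentage: 2d/(2m) = d/m.
- In newtons: m × d/m = d.
- Limits: m − d and m + d, which are the confidence limits again.

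With invented values of mean 40 and limits 35 and 45, the formula returns 35 and 45. The article does not say what the confidence interval refers to. As it is centred on the mean, I read it as the interval for the mean.

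**What such a range does to individuals (illustration)**

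The plan gives no figure to reproduce. Assumptions: thresholds are normal, later patients come from the same population as the calibration sample, the threshold is one level's calibrated force, and the interval is centred on the true mean. The number n supplying the calibration values is not stated, so a range is shown.

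- Half-width in SD units: h = t(0.975, n − 1)/√n.
- Share inside: 2Φ(h) − 1.
- Patients assessed to fill 24 Part 2 places: 24/share, rounded up.

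| n | h | Share inside | Assessed for 24 places |
|---|---|---|---|
| 6 | 1.049 | 71% | 34 |
| 15 | 0.554 | 42% | 58 |
| 24 | 0.422 | 33% | 74 |
| 48 | 0.290 | 23% | 106 |

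The row for 48 treats both sides of 24 people as independent, which overstates the information. The share inside falls as the calibration sample grows, which shows that the interval measures the precision of a mean and not the spread of patients.

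**A more lenient reading**

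Suppose the range runs from the low level's lower limit to the high level's upper limit. If the threshold is the high-level force and almost nobody lies below the bottom limit, the share inside is Φ(h), or 66% at n = 24. If the threshold is the medium-level force and the levels are well separated, almost everyone could pass. The loss therefore depends on two definitions that the text does not give.

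**The case against.** The strongest reply is that this is mainly a matter of placement. The rule, its timing and its consequence are all stated in 2.4.2. The study is single-centre, and 2.7 refers to a research manual and pre-job training that we cannot see. No stated sample size, power, alpha or endpoint depends on the rule. This limits the severity but does not remove the conflict: 2.2.2 does not merely omit the criterion, it states that the lists differ only in (h).

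The reply on size is stronger. The calibration number and the meaning of bearing threshold are not given, so no minimum loss can be asserted.

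A reader might infer that Part 3 patients are screened too, which would change to whom the ODI result applies. The documents do not support that. The rule stands under the Part 2 heading, and neither 2.2 nor 2.4.3 shows a screen for Part 3. Only if all 24 Part 2 patients supplied the calibration values would later patients have to be Part 3 patients, and nothing says that they did. Even then, a screen applied before allocation would leave the randomised comparison valid.

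A reader might also point to Table 2, which has the row "Confirm exclusion criteria" at the first visit and no threshold row. That carries little weight: the table also omits the pressure calibration itself, and the first-visit specialised examination could include a threshold check.

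**Conclusion.** The contradiction between 2.2 and 2.4.2 on Part 2 eligibility holds on the text alone and needs no assumption. The rule also cannot be applied as written, because one range is cited where three intervals are derived. That the limits suit a mean and not individuals follows from the formula, given the ordinary reading of the confidence interval.

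The size is illustrative only. Under a single-level reading with normal thresholds, about 29% would be excluded at n = 6, 67% at n = 24 and 77% at n = 48; under a span reading the loss could be far smaller. For Part 3 the plan shows no screen, and the point there is only that one clarifying sentence is needed. This should be corrected, but it does not threaten the Part 3 comparison.

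**What to change.** Choose one of two routes.

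1. Delete the threshold sentence in 2.4.2 and rely on the limit already stated there, that the high level is applied only within the participant's own pain tolerance.
2. Keep the screen, and list it once in 2.2.2 as item (i), Part 2 only. Reword the opening of 2.2.2 so that (h) is absent from Part 2 and (i) applies only to Part 2. In 2.4.2, state who supplied the calibration values, name the interval, and name the level at which the threshold is measured. Base the limits on individual spread, such as a reference or tolerance interval, in place of the confidence interval of the mean.

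Under either route, add one sentence to 2.4.3 saying whether any threshold screen applies to Part 3.

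The cost is wording in 2.2.2, 2.4.2 and 2.4.3, with no measurement beyond what the present screen would need. The downside is that patients with more varied tolerance are enrolled, so the individual tolerance limit must protect them.
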